### Description of trial visits

The screening visit marks the start of the study. At this visit, each potential participant will be comprehensively informed about the clinical trial prior to enrollment. The information is provided in-person by a medical member of the trial team and in printed form in a detailed patient information sheet. At this visit, inclusion and exclusion criteria will be reviewed, and demographic data, medical history, and secondary diagnoses will be collected if the patient gave informed consent. In addition, participants will undergo a physical examination (including ECG) and laboratory testing will occur, as well as recording of vital signs and body weight.

The following data will be acquired:

demographic data (sex, age, body weight, height, BMI)medical history, secondary diagnoses, concomitant medicationdiabetes history, diabetes aidsglycemic parameters (blood glucose determination, HbA1c, C-peptide, fructosamine)vital signs (pulse, blood pressure, temperature, body weight)physical examination resultsEORTC QLQ-C30/Pan26 questionnaire [20]ECGblood and urine examinationpregnancy testtumor markers CA19−9 and CEA

All other visits will be performed postoperatively. A total of 10 postoperative visits are planned. The participant timeline is shown in the corresponding SPIRIT figure (Fig 2). A detailed visit schedule and all data collected are attached in supplementary materials (S1 Table).

**Fig 2 pone.0327949.g002:**
[figure not shown]
Standard Protocol Items: Recommendations for Interventional Trials (SPIRIT) figure for participant timeline. Abbrevations: IAT, intraportal islet autotransplantation; QoL, quality of life.

### Data management, statistics and quality assurance

#### Data management and quality assurance.

The data obtained in this clinical trial will be documented in an eCRF based on the study software MACRO 4.8 (or higher). The eCRF will be generated by Coordination Center for Clinical Trials Dresden (KKS Dresden). The correctness of the documented data will be checked by reconciliation of the source data with the documentation by the monitor of the KKS Dresden according to the specifications of the monitoring plan. In case of discrepancies, queries will be made in the eCRF and will be answered by authorized members of the review group. The eCRF itself contains range, validity, and consistency checks, so that potential errors can already be detected by the database during data entry. The Coordination Center for Clinical Trials Dresden will check the entered data according to the data management plan and will issue appropriate queries in case of discrepancies. Upon completion of the check, the database will be closed after all data has been entered and queries have been resolved. All data management processes will be documented and the documentation will be stored in the TMF.

#### Reporting adverse events.

The safety of both treatment methods is verified by documenting all AEs and SAEs that occur.

The frequency and type of (S)AEs are recorded according to the Common Terminology Criteria for Adverse Events (CTCAE; version 5.0, 2017). Of particular interest here are (serious) adverse events that can at least probably be attributed to the transplant.

The criteria for assessing causality correspond to the WHO-UMC criteria. These parameters are checked as part of the questioning and clinical examination of the patient during each visit after intervention/transplantation. 

#### Statistical methods.

The data collected within this exploratory trial will provide the basis for a subsequent confirmatory controlled study. Therefore, no formal sample size estimation was performed. Assuming an event rate of about 60 percent, a sample size of 30 patients (15 individuals per treatment group) allows for the detection of a hazard ratio of approximately 0.31 (two-sided significance level of 10%, power of 80%). Assuming a drop-out rate of 5%, 16 patients per treatment group will be included. 

The main analysis will be performed after completion of the two-year follow-up period (including data collection and cleaning) in the entire intention-to-treat population. No interim efficacy analyses are planned in this study. All analyses will be performed using SAS 9.4 or higher.

The confirmatory analysis of the primary endpoint and the analysis of the secondary endpoints will be performed according to ICH E9 [21] using the full analysis set (intention-to-treat population) and follow the intention-to-treat principle. The full analysis set will include all randomized patients.

##### Per-protocol population

The per-protocol population will include all patients in the intention-to-treat population without any serious protocol deviation.

##### Safety analysis set

The safety analysis set includes all patients in whom the investigational therapy was used.

For long-term oncologic outcomes (survival analyses), patients lost to follow-up and patients deceased within the observation period will be censored. A per-protocol analysis is planned for sensitivity analysis.

The primary endpoint (time between surgery and day of “fit for adjuvant treatment”) is defined as the interval between day of surgery and day of oncologists decision that patient is fit to start the administration of adjuvant chemotherapy, measured in days. It will be analyzed using Kaplan-Meier estimators (with a two-sided confidence level of 90 percent). Comparison of the primary endpoint between the treatment groups will be performed using the log-rank test. In case of proportional observed hazards in the control and treatment groups, a Cox proportional-hazards model will be used to examine which covariates have an impact on the hazard ratio of the two treatments. Safety analysis will include the frequency of (serious) adverse events in the safety analysis set. Annual safety analyses will be performed in accordance with regulatory requirements. Frequencies and types of adverse events (AE, SAE) will be summarized as relative frequencies (proportions) and, if applicable, the occurrence of specific events (at the patient level) of the two groups will be compared using chi-square test. QLQ-C30/Pan26 questionnaires will be analyzed using a mixed model with the patient as a random factor analysis, including comparison of changes in quality of life over time between the two treatment groups, and respective covariates potentially impacting quality of life within each of the two treatments. Exact Chi-Square test will be used to analyze perioperative morbidity and mortality. Metabolic outcome over time will be analyzed using a mixed model with the patient as a random factor. To analyze the oncologic outcome, a Cox regression model will be used.

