### Description of the investigational product

The investigational medicinal product consists of isolated and purified autologous pancreatic islets and will be manufactured, tested and released patient-related under GMP conditions according to the German Drug and Drug Substance Manufacturing Regulation (Arzneimittel- und Wirkstoffherstellungsverordnung, §16) under the responsibility of the University Hospital Carl Gustav Carus at the Technical University of Dresden.

The pancreatic islets are isolated and purified from the patient’s own pancreatic tissue according to §13 Medicines Act (AMG). The pancreatic resection is performed in accordance with §20b AMG. The isolation process takes place after preparation of the tissue (liberation of surrounding fatty/binding tissue) by distension with an enzyme mixture (collagenase, neutral protease, DNAse) via the pancreatic duct and initiation of the enzymatic digestion process by heating to 35°C and mechanical support. After release of the intact islet cell clusters from the surrounding tissue, the digestion process is stopped by cooling the system and adding albumin-containing medium. Subsequently, the tissue suspension is washed several times, and separation of islet cell clusters and exocrine tissue components is achieved by density gradient centrifugation. The purified islet preparation is transferred to transplantation medium after repeated washing steps. The process is accompanied by defined in-process controls. 

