### Treatment regimen

In the control arm, oncological PD is performed as pylorus-preserving pancreatic head resection (PPPD) or as classic Whipple procedure with the only requirement for the form of reconstruction being that the pancreatic reconstruction must be to the jejunum. In the intervention arm, oncological total pancreatectomy is performed. This procedure may or may not include simultaneous splenectomy/partial gastric resection, depending on the situs. In the case of total pancreatectomy, application of the investigational drug then follows once after the above-mentioned islet cell isolation and purification steps. Multiple or re-transplantation is not intended in the context of this study. The extension of the surgical procedure (e.g., oncological reasons) is explicitly not limited by the study protocol.

IAT is performed under general anesthesia at the end of the pancreatic resection. For this, portal vein is accessed and punctured with a three-lumen central venous catheter (CVC). The CVC is advanced into the right portal vein branch. The correct position is checked and documented intraoperatively using ultrasound. A continuous pressure system is connected to the CVC to measure portal vein pressure. After establishing the appropriate infusion systems, the preparation is infused by gravity over a period of approximately 30 minutes. The portal vein pressure is continuously monitored. In case of a pressure increase of >50%, the infusion is slowed down or paused and continued after normalization of portal vein pressure. In case of an irreversible pressure increase above 100%, the infusion is stopped and the remaining preparation is withdrawn.

All study patients receive standard postoperative interdisciplinary follow-up in the surgical intensive care unit to guarantee specific monitoring of islet function and adjustment of diabetes treatment, if applicable.

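### As defined, the safety analysis set contains no pancreatoduodenectomy patients, so the planned two-group adverse-event comparison cannot be run in it, and the same adverse-event data are also assigned to a second population

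*Protocol article*

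**What the plan says.** The analysis-set definitions in the protocol article give: "The safety analysis set includes all patients in whom the investigational therapy was used". The text under the same heading then places the safety analysis there: "Safety analysis will include the frequency of (serious) adverse events in the safety analysis set". It adds that, where applicable, "the occurrence of specific events (at the patient level) of the two groups will be compared using chi-square test".

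Three other places determine who is in that set:

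- Description of the investigational product: "The investigational medicinal product consists of isolated and purified autologous pancreatic islets".
- Treatment regimen, intervention arm: "In the case of total pancreatectomy, application of the investigational drug then follows once after the above-mentioned islet cell isolation and purification steps".
- Treatment regimen, control arm: "In the control arm, oncological PD is performed as pylorus-preserving pancreatic head resection (PPPD) or as classic Whipple procedure". No islets are given.

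The section on reporting adverse events sets the aim: "The safety of both treatment methods is verified by documenting all AEs and SAEs that occur". The Outcome section lists the frequency and type of adverse events among the secondary outcomes. Statistical methods assigns secondary endpoints to the full analysis set, meaning every randomised patient.

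**The concern.** A safety set normally holds everyone exposed to any study treatment, control included, so that harms can be set against a comparator. This one is defined by use of the investigational therapy, and in this article only the islet product is called investigational. Taken at its word, the definition removes the comparator from the set in which the comparison is to be made.

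Comparative safety is a main product of this pilot. The Introduction wants safety data set against the current surgical standard, and the Discussion makes feasibility and safety the basis for a confirmatory trial. A one-arm table shows how often events occurred after TP with islets. It cannot show whether that is more or less often than after high-risk PD.

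There is a second, smaller effect. A patient randomised to TP with islet autotransplantation who has the pancreas removed but receives no islets may fall outside the set. Events in such a patient belong to the safety record of the strategy being tested.

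**Working it through.** **Inputs.** 32 patients randomised 1:1 (Trial design and timeline). 15 per group, 5% drop-out, 16 per group included (Statistical methods).

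**The plan's own count.** 15 / (1 − 0.05) = 15.8, rounded up to 16 per arm; 2 × 16 = 32. This reproduces. The sample-size statement for the primary endpoint is not affected by this point.

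**Membership under each reading of the term.** Counts assume that every patient is treated as allocated.

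| Reading of investigational therapy | TP, islets infused | TP, no islets | PD | Set (TP vs PD) |
|---|---|---|---|---|
| The islet product (the article's own use of the word) | in | out | out | up to 16 vs 0 |
| The whole strategy of TP plus islets | in | arguably in | out | 16 vs 0 |
| Any study treatment | in | in | in | 16 vs 16 |

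Only the third reading brings PD into the set. The article never calls PD investigational; it calls it the control arm and the current standard.

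**The test on 16 versus 0.** The expected count in a cell is row total × column total / N. Suppose, for illustration, that 8 of 16 TP patients have a given event. The PD row total is 0, so both of its expected counts are 0 × 8 / 16 = 0. Each PD cell contributes (0 − 0)² / 0, which is undefined. Run on the table [8, 8; 0, 0], a standard chi-square routine stops with an error reporting a zero expected frequency. The result does not depend on the illustrative 8, because an empty row always gives zero expected counts.

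**The two populations side by side.**

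- Route 1, the safety analysis: adverse events in the safety set, up to 16 vs 0.
- Route 2, the secondary outcome: adverse events in the full analysis set, 16 vs 16.

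The article does not say which route governs the between-arm comparison. The sentence that mentions the chi-square test follows directly on the safety-set route.

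**After the fix.** All randomised patients in whom either operation was started, grouped by procedure received: 16 vs 16 if treated as allocated. At the planned 5% drop-out, 0.95 × 16 = 15.2, or about 15 vs 15. The table has two rows and the test can be computed.

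**The case against.** The strongest defence is that the decisive term is undefined. The article speaks of an investigational medicinal product and an investigational drug for the islets, but of investigational therapy in the set definition. That could mean the whole TP-plus-islets strategy, or study treatment in general. The last meaning fits the mention of two groups and of both methods. This shows what the authors probably intended. It does not rescue the text: the strategy reading still leaves PD out, and the general reading has no support in how the article uses the word. Making the comparison only where applicable puts no control patients into the set.

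The defence also limits the point in ways that stand:

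- A reader might infer that control-arm safety data are lost or can never be compared. The documents do not support that. All events in both arms are documented, adverse events are a secondary outcome in all randomised patients, and perioperative morbidity and mortality have their own exact chi-square test.
- A reader might infer that a known share of TP patients drops out of the tables. The article gives no rate of TP without infusion and does not describe failed isolation. It describes an infusion being stopped, and a partly infused patient still had the product used. The gap is possible because the product must be tested and released before use, but its size is unknown.
- A reader might take the particular interest in transplant-attributed events as a restriction. It is an emphasis only, since the same section documents every event.

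The article condenses a full protocol that is not shown and may word the set differently. The point here is not something left out. The article fixes a definition, and that definition conflicts with the analysis beside it.

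**Conclusion.** The point holds as an internal contradiction. Read as written, the safety set has one arm, the adverse-event analysis is placed in it, and a two-group test is planned that cannot be computed there. The article also assigns the same data, as a secondary outcome, to all randomised patients. The two instructions lead to different tables: 16 vs 0 against 16 vs 16.

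The counts rest on two assumptions: that the term refers to the islet product or to the TP-plus-islets strategy, and that patients are treated as allocated. They are not bounds. Set membership follows treatment used, so any crossover would shift them. The primary endpoint, sample size, randomisation and data collection are not affected.

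**What to change.** Replace the definition with one along these lines:

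> The safety set comprises all randomised patients in whom either study operation was started, that is, PD, or TP with or without islet infusion. Patients are analysed by the procedure received, and TP without infusion is shown separately.

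Name this set as the single population for the between-arm comparison of adverse and serious adverse events. Add to the sentence on secondary endpoints that adverse events are the exception to the full analysis set. A subset of islet recipients may be kept for describing transplant-attributed events within that arm.

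The cost is wording in the protocol or analysis plan. No new data are needed, because events are already recorded in both arms, and the sample size does not change. Recruitment began in January 2025, the trial is open-label and annual safety analyses are planned, so the change should be made promptly and dated.

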**Methods and analysis:**

XANDTX is a single-centre randomized controlled pilot trial comparing high-risk PD with TP and simultaneous IAT in patients with periampullary cancer. After screening for eligibility and obtaining informed consent, a total of 32 adult patients will be intraoperatively randomized in a 1:1 ratio. The primary hypothesis is that TP with IAT prevents POPF-associated complications and leads to a shorter period to initiation of adjuvant therapy and a higher overall rate of adjuvant therapy administration.

Secondary endpoints include perioperative morbidity and mortality, metabolic outcome, quality of life (QoL) and oncological long-term outcome. Each patient will be followed up for 5 years.

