**Fig 1 pone.0327949.g001:**
[figure not shown]
Study flowchart.

The recruitment start for this study was in January 2025. The planned recruitment period is 24 months. The individual follow-up time after surgery is 60 months, resulting in a study duration of 84 months, after which results are expected. The trial will be reported according to the Consolidated Standards of Reporting Trials (CONSORT) Extension for Randomized Pilot and Feasibility Trials [19].

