A potential risk of IAT in patients with pancreatic malignancy is the transfer of dysplastic cells and induction of liver metastases by intraportal transplantation. During the islet isolation process, endocrine cellular portions of the pancreas are enriched, but complete elimination of ductal cells cannot be guaranteed. However, studies from Balzano *et al.* demonstrated that the oncologic outcome after IAT in patients with malignant disease is not worse compared with patients treated according to standard protocols [10,29]. Moreover, in the case of standard pancreatic head resection, pancreatic parenchyma with potentially dysplastic cells remains in situ. Therefore, the purification and thus significant reduction of exocrine/ductal fractions performed in the course of islet isolation and transplantation can be considered equivalent from an oncological point of view with regard to the amount of potentially malignant cells remaining in situ.

The XANDTX pilot trial will aim to provide feasibility and safety data that will generated a hypothesis and basis for a subsequent confirmatory controlled study that has the potential to provide practice changing data.

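### The censoring rule for the long-term oncologic analyses removes deaths, so any endpoint that counts death as an event loses those events

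*Protocol article*

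**What the plan says.** The rule stands in the protocol article, Statistical methods, under Safety analysis set: "For long-term oncologic outcomes (survival analyses), patients lost to follow-up and patients deceased within the observation period will be censored". The same section names the model: "To analyze the oncologic outcome, a Cox regression model will be used".

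The Abstract lists as secondary endpoints, among others, "quality of life (QoL) and oncological long-term outcome. Each patient will be followed up for 5 years". Trial design and timeline confirms the duration: "The individual follow-up time after surgery is 60 months". The Outcome section lists long-term oncologic outcome as a secondary parameter and places the time from surgery to actual start of chemotherapy within it. It does not name overall survival or disease-free survival.

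The Discussion gives the oncologic concern behind this outcome, the possible "induction of liver metastases by intraportal transplantation", and concedes that ductal cells may not be completely removed during islet isolation.

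Deaths also enter the analysis in two other places. Perioperative morbidity and mortality are compared with an exact chi-square test, and all adverse and serious adverse events are documented and summarised.

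**The concern.** Censoring is meant for patients whose event has not been observed when their follow-up ends. In overall survival a death is the observed event. In disease-free survival a death without recurrence is also an event. A rule that censors deaths in all long-term survival analyses deletes the information those analyses exist to use.

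The article sets out to supply oncologic as well as surgical safety data on infusing islets from a cancer-bearing organ into the portal vein, and to serve as the basis for a confirmatory trial. If the rule were followed literally, the planned time-to-event analysis could not compare long-term survival between the arms.

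This is a stated rule that is wrong, not a detail left to a statistical analysis plan. A plan that handled overall survival correctly would have to contradict it.

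**Working it through.** **1. The plan's own figure.** The only planning figure concerns the primary endpoint: "Assuming an event rate of about 60 percent, a sample size of 30 patients (15 individuals per treatment group") allows "detection of a hazard ratio of approximately 0.31 (two-sided significance level of 10%, power of 80"%).

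- Events: 0.60 × 30 = 18.
- Schoenfeld: HR = exp(−√(4 × (z₀.₉₅ + z₀.₈₀)² / events)) = exp(−√(4 × (1.645 + 0.842)² / 18)) ≈ 0.310. Power at HR 0.31 is 79.9%.
- Drop-out: "Assuming a drop-out rate of 5%, 16 patients per treatment group will be included". 15 / 0.95 = 15.8, rounded up to 16 per arm, 32 in total.

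The figure reproduces. The point below does not depend on it; it supplies only the 32 patients.

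**2. Overall survival under the written rule.** Let D be the number of deaths within the observation period. Each is coded censored, as is each loss to follow-up, so the events are D − D = 0 for any D. The Kaplan-Meier curve then has no steps. The Cox partial likelihood is a product over event times; with none, it does not depend on the hazard ratio, and nothing can be estimated. A simulated set of 32 patients with 23 deaths behaved accordingly: no Kaplan-Meier event times, and a log-rank test that failed on a singular variance matrix. This only confirms what the definition implies.

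The article gives no 5-year mortality. Over an assumed range:

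| Assumed 5-year mortality | Deaths among 32 | Events under the rule |
|---|---|---|
| 20% | 6.4 | 0 |
| 40% | 12.8 | 0 |
| 60% | 19.2 | 0 |
| 80% | 25.6 | 0 |

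**3. Disease-free survival under the written rule.** Assumptions, none from the article: 5-year event risk p of 50% or 70%; share s of first events that are deaths without recurrence, 10% to 30%; constant hazards. Events lost = 32 × p × s. The Kaplan-Meier value at 5 years with those deaths censored is (1 − p)^(1 − s), against a true value of 1 − p.

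| p | s | Events | Lost | True 5-year value | With deaths censored |
|---|---|---|---|---|---|
| 50% | 10% | 16.0 | 1.6 | 50% | 53.6% |
| 50% | 20% | 16.0 | 3.2 | 50% | 57.4% |
| 50% | 30% | 16.0 | 4.8 | 50% | 61.6% |
| 70% | 10% | 22.4 | 2.2 | 30% | 33.8% |
| 70% | 20% | 22.4 | 4.5 | 30% | 38.2% |
| 70% | 30% | 22.4 | 6.7 | 30% | 43.1% |

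**4. Time to recurrence.** Here censoring at death is how a cause-specific Cox model is fitted, so the rule does no damage to the hazard ratio as a cause-specific quantity. The cumulative scale is different. Under the same assumptions the true cumulative incidence of recurrence is p × (1 − s), while one minus Kaplan-Meier gives 1 − (1 − p)^(1 − s). For p = 50%, s = 30%: 35% against 38.4%. For p = 70%, s = 30%: 49% against 56.9%. One minus Kaplan-Meier overstates recurrence.

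**5. Is the rule limited anywhere?** The Outcome, Statistical methods and Discussion sections contain no statement that makes death an event in a time-to-event analysis, restricts the rule to recurrence or to non-cancer deaths, or introduces a competing-risk method.

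**The case against.** The strongest reply is that the article names neither overall nor disease-free survival. The one component it does name, time to actual start of chemotherapy, can properly be censored at death in a cause-specific analysis, and so can time to recurrence. This stands, and it makes the zero-event result conditional. It does not rescue the sentence, which applies to all long-term oncologic outcomes, describes them as survival analyses and exempts none.

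Second, deaths are counted elsewhere, through perioperative mortality and serious adverse events. A reader might infer that the trial could show nothing about mortality; that goes too far. But a perioperative proportion and an adverse event table do not replace a comparison of survival over 60 months.

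Third, a reader might infer that an arm with more early deaths would look better on recurrence. The documents do not support this as a general statement. A censored death adds no event, but it also leaves the risk set, so the cause-specific hazard is not lowered mechanically. Bias in that direction would require that the patients who die would otherwise have recurred more often, and nothing in the article bears on that.

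Fourth, the sentence may be a drafting slip: it omits patients alive at the end of follow-up, who are the usual censored group. It is also unlikely that a statistician would run overall survival with no events. Both are plausible, but the published rule still needs correcting.

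**Conclusion.** The rule is wrong as written for every endpoint in which death is an event. For overall survival the loss is total (0 events, no estimable Cox hazard ratio) and follows by definition, without any assumed mortality. For disease-free survival every death without recurrence is lost; about 1.6 to 6.7 of 16 to 22.4 events is an illustration that rests on the assumed event risks, shares and constant hazards above.

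Both results presuppose that these endpoints are among the survival analyses. The article does not say so outright, but its description of the outcomes, the 60-month follow-up and the oncologic safety aim make this the natural reading.

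The point concerns a secondary outcome of an exploratory pilot. The rule is confined to long-term oncologic outcomes, so it does not touch the primary endpoint, its log-rank test or the sample size figure. It should nonetheless be corrected before analysis, because oncologic safety is one of the trial's stated purposes.

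**What to change.** Replace the sentence with a rule for each endpoint:

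- **Overall survival:** death from any cause is the event; patients alive or lost to follow-up are censored at last contact.
- **Disease-free survival:** first recurrence or death from any cause is the event; patients event-free at last contact are censored.
- **Time to recurrence and time to start of chemotherapy:** patients may be censored at death in a cause-specific Cox model. Cumulative incidence is estimated with death as a competing event (Aalen-Johansen), not as one minus Kaplan-Meier.

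The cost is the rewording of one sentence, carried through to the analysis plan. No new data are needed, and the sample size and primary analysis stay as they are.

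### The only planned between-arm effect estimate for the primary endpoint depends on observed proportional hazards, and its model is assigned a covariate question that about 18 events can hardly answer

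*Protocol article*

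**What the plan says.** The analysis of the primary endpoint is described in the protocol article under the Safety analysis set heading. It has three steps.

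- Kaplan-Meier estimation with a 90% two-sided confidence level, without condition.
- A log-rank comparison of the arms, without condition.
- A Cox model, with a condition and a purpose attached. The condition is "In case of proportional observed hazards in the control and treatment groups". The purpose follows in the same sentence: "a Cox proportional-hazards model will be used to examine which covariates have an impact on the hazard ratio of the two treatments".

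No other between-arm effect measure is named for this endpoint, and the article does not say what replaces the Cox model if the condition fails.

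The Statistical methods section gives the role of the trial: "The data collected within this exploratory trial will provide the basis for a subsequent confirmatory controlled study". It justifies the size on the hazard-ratio scale: 30 patients with about 60% events "allows for the detection of a hazard ratio of approximately 0.31", at a two-sided 10% level and 80% power. It then adds for drop-out: "Assuming a drop-out rate of 5%, 16 patients per treatment group will be included".

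**The concern.** Two features of the Cox sentence do not fit the purpose of the trial.

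First, the hazard ratio is the scale on which the pilot is sized, yet it is produced only if the same small data set looks proportional. A pilot that feeds a confirmatory trial should deliver a between-arm effect size with an interval in every case. As written, one branch of the plan delivers a between-arm p-value and two separate curves, but no estimated contrast.

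Second, when the model is fitted, its stated task is not to estimate the treatment effect. It is to find covariates that affect the treatment hazard ratio. Read literally, that is effect modification, which needs far more events than a main effect. At stake is the quality of what is passed on to the next trial: possibly no effect estimate, or attention drawn to covariate findings that the data cannot support.

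**Working it through.** **Inputs, all from the Statistical methods section.** 30 evaluable patients, 15 per arm; event rate about 60%; two-sided 10% level; 80% power; 32 randomized after 5% drop-out. The normal quantiles are 1.645 (two-sided 10%) and 0.842 (80% power), which sum to 2.487.

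**1. Reproduce the plan's own figure.** Events d = 30 × 0.60 = 18. With 1:1 allocation, Schoenfeld's formula gives SE(log HR) = 2/√d = 2/√18 = 0.471. The detectable HR is exp(−2.487 × 0.471) = 0.31, which matches the article. So 18 is the number of events implied by the plan, and the stated 0.31 is not in dispute. Those events just reach 80% power for one main effect of that size.

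**2. What the same events give for effect modification.** With a balanced binary covariate, each of the four arm-by-covariate cells holds about d/4 events. The variance of the log ratio of hazard ratios is then 4 × 1/(d/4) = 16/d, so SE = 4/√18 = 0.943.

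- Smallest detectable ratio of hazard ratios: exp(2.487 × 0.943) = 10.4.
- Power for an interaction as large as the planned main effect (0.31): |ln 0.31| / 0.943 = 1.171/0.943 = 1.24, which gives about 35%. A simulation of the Cox model with 30 patients and 18 events gave 31%.
- Events needed for an interaction of 0.31: 16 × 2.487² / 1.171² ≈ 72, four times 18.

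**3. Sensitivity to the event rate.**

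| Patients, event rate | Events | Detectable ratio of HRs | Power at 0.31 |
|---|---|---|---|
| 30, 50% | 15 | 13.0 | 31% |
| 30, 60% | 18 | 10.4 | 35% |
| 30, 70% | 21 | 8.8 | 38% |
| 32, 100% | 32 | 5.8 | 50% |

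A covariate split 30/70 is worse: about 13-fold at 18 events. The conclusion does not hinge on the 60%.

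**4. How informative the proportionality condition is.** The article names no check, so this step assumes a 10%-level test on Cox residuals. In 3,000 simulated trials per scenario (30 patients, 18 events), it flagged a hazard ratio falling from 3 to 1 in about 19% of trials, and one falling from 3 to 0.5 in about 25%. It also rejected about 10% of truly proportional trials. Such a check does little to separate the two situations, yet it would decide whether an effect estimate is reported.

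**5. What remains if the Cox model is not fitted.** The Kaplan-Meier curves and the log-rank test remain. A difference in medians is not a safe substitute. As an illustration, take 60% as the pooled event rate at the end of observation, equal arms and a constant ratio of 0.31. Event-free proportions then satisfy S_slow = S_fast^0.31 and S_fast + S_slow = 0.80. Trying S_fast = 0.20 gives 0.20^0.31 ≈ 0.61 and a sum of 0.81. So about 80% of one arm and 40% of the other would have events, and the slower arm would not reach its median.

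**The case against.** Much of the case on the other side is sound.

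- A reader might infer that only a log-rank p-value is left under non-proportional hazards, or that the primary comparison itself is conditional. The text supports neither. The Kaplan-Meier curves with 90% intervals and the log-rank test are always produced, and the curves can inform a later design. What is not guaranteed is a between-arm contrast with an interval.
- A reader might infer a data-driven covariate screen with a high false-positive rate. At the 10% level, 3, 5 or 8 independent null covariates would give at least one false hit with probability 1 − 0.9^k = 27%, 41% or 57%. But the article states no number of covariates, no selection rule and no threshold for them, so these figures rest on assumptions. A claim that intervals would be too narrow after selection has no basis in the text either.
- The 10-fold figure applies only if the sentence means effect modification. It could loosely mean covariate adjustment, which costs fewer parameters. The wording favours the first reading but does not settle it.
- The width of the treatment interval (HR divided or multiplied by exp(1.645 × 0.471) = 2.17) is not a harm of the present wording. It would be the same under the fix.
- That hazards will be non-proportional because fistula acts early is plausible, but no figure in the article shows it. On the simulation above, a formal test would usually let the Cox model be fitted.
- The covariate list and the choice of proportionality check may stand in a statistical analysis plan that is not shown. Their absence is not the point.
- The trial is exploratory, and looking at covariates in a pilot is ordinary. This softens the consequence, although the article also calls the analysis of the primary endpoint confirmatory.

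What survives is the rule that the article does state: a condition on the only effect estimate, and a purpose for that model other than estimating the treatment effect.

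**Conclusion.** The point holds in this limited form. Followed as written, the plan may end without a between-arm effect size and interval for the primary endpoint, although the pilot is sized on a hazard ratio and is meant to supply the basis for a confirmatory trial. When the Cox model is fitted, an effect-modification question could be answered only for about a 10-fold ratio of hazard ratios, or about 6-fold if every one of 32 patients had an event. These sizes assume a balanced binary covariate, Schoenfeld-type variances and the article's own level and power; 18 events is derived from its inputs, not stated. The chance of false covariate findings cannot be given, because the number of covariates is not stated. The log-rank comparison and the stated 0.31 are unaffected. The change is worth making because it is nearly free, but the present wording does not invalidate the primary comparison.

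**What to change.** Replace the conditional Cox sentence with three statements.

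1. The hazard ratio from a Cox model with treatment as the only term is reported with its 90% CI whether or not hazards look proportional. Without ties, the score test of this model is the log-rank test already planned, so it is the natural estimate to accompany that test. Proportionality may be described, but it does not decide what is reported.
2. The difference between arms in restricted mean time to fitness, up to one day fixed before the data are seen, is reported with its 90% CI. This contrast does not need proportional hazards. Patients who die before being declared fit should be handled by the same rule as in the Kaplan-Meier analysis.
3. Any examination of covariates is labelled descriptive, and the sentence says whether it concerns adjustment or effect modification.

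The cost is wording and a few lines of code, with no change to patients, visits or sample size. The downside is slightly more analysis work and less weight on the covariate results.
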